### Inclusion criteria

Criteria for inclusion in the study are 1) patients above 1 month and less than 19 years of age, 2) end-stage renal disease with manual or automated continuous peritoneal dialysis as maintenance treatment modality, 3) a fill volume approximately of 1100 ml/1.73 m^2 ^body surface area, 4) the most recent episode of PD-associated peritonitis, if any, occurred more than 3 weeks ago, 5) signed informed consent by parent/guardian, with a subject aged > 7 years also signing an age-appropriate assent form.

### Exclusion criteria

Criteria for exclusion from the study are 1) reduced efficiency of peritoneal dialysis due to anatomic anomalies or intraperitoneal adhesions, 2) uncontrolled hyperphosphatemia, 3) severe pulmonary, cardiac, hepatic or systemic disease including any kind of malignancy, and 4) current or recent (within 30 days) exposure to any investigational drug.

### Exit criteria

Reasons for permanently discontinuing the study medication are 1) renal transplantation, 2) switch to hemodialysis due to PD technique failure, 3) patient/parent withdrawal of consent of participate, 4) patient moving out of the area to a location with no participating center within reasonable distance, and 5) a severe adverse event.

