**Table 1 T1:** 

	Balance 1.5%	Balance 2.3%	Balance 4.25%	Bicavera^® ^1.5%	Bicavera^® ^2.3%	Bicavera^® ^4.25%
Sodium (mmol/l)	134	134	134	134	134	134
Calcium (mmol/l)	1.75	1.75	1.75	1.75	1.75	1.75
Magnesium (mmol/l)	0.5	0.5	0.5	0.5	0.5	0.5
Chloride (mmol/l)	101.5	101.5	101.5	104.5	104.5	104.5
L-Lactate (mmol/l)	35	35	35	-	-	-
Bicarbonate (mmol/l)	-	-	-	34	34	34
Glucose-monohydrate (g/l)	15	23	42.5	15	23	42.5
Osmolarity (mosmol/l)	358	401	511	358	399	509
PH	7.4	7.4	7.4	7.4	7.4	7.4

Any kind of concomitant medication during the run-in period and the study period will be documented in the case report form with respect to type, dosage and mode of delivery. In case of peritonitis (defined by cloudy effluent, white blood cell count greater than 100/mm^3 ^with more than 50% polymorphonuclear leukocytes), treatment will be given intraperitoneally according to international pediatric guidelines [24] using cefazoline and ceftazidime in patients with mild peritonitis and a glycopeptide/ceftazidime combination in patients with defined risk factors for severe course and poor outcome.

Bicarbonate supplementation will be discontinued at start of the run-in period and only re-instituted if blood bicarbonate levels drop below 17 mmol/l despite sufficient dialysis efficacy. The recommended dosage is 0.5 mmol/kg/day divided into 3 doses.

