### Clinical safety monitoring

An adverse event is defined as any untoward medical occurence in a patient who takes the study medication. It does not necessarily have a causal relationship with this treatment. This may be an unfavourable and unintended sign, symptom or disease, which is observed after exposure to the study medication, whether or not considered related to the treatment. Moreover, the participating investigators will report all treatment-emergent adverse events that are observed on the online adverse event form. This applies regardless of the clinical significance or the assessment of study drug causality. In this trial, such adverse events may include inflow pain, severe changes of the state of hydration, abnormal electrolyte and glucose blood levels, peritonitis, abdominal hernia, and allergic reactions.

A severe adverse event or reaction is any untoward medical occurrence that a) results in death, b) is life-threatening, c) requires inpatient hospitalization or prolonges an existing hospitalization, or d) results in persistent or significant disability/incapacity.

Any serious adverse event, whether or not considered related to the study medication, and any unexpected drug reactions with significant hazard to the patient population will be reported to the responsible safety assessor at Fresenius Medical Care by phone or by fax within 24 hours following first knowledge of the event. Alternatively the clinical monitor may be informed. This information will be forwarded to and evaluated by the safety monitoring committee, and reports of serious adverse reactions will be disseminated to all participating centers for submission to their respective institutional review boards. Fresenius Medical Care is responsible for passing on the information to relevant supervisory authorities.

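### The completers-only ANOVA drops children who already have on-fluid PETs, and the loosely worded adverse-event exit can avoidably add to that loss

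*Protocol article*

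**What the plan says.** All references are to the protocol article.

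- **Statistical approach** names two strategies for D/P creatinine and ranks neither. The first is a repeated-measures ANOVA confined to children who finish 10 months on the study fluid. The second is a Kaplan-Meier analysis of time to a rise of at least 7.5%, open to everyone who began study fluid. Secondary outcomes are handled the same way.
- **Study design** describes an open-label trial with PETs at randomization (on conventional fluid) and after 3, 6 and 10 months on the assigned fluid.
- **Sample size estimation** asks for 15 per group, assumes 50% drop-out from transplantation and other causes, and so enrols 60. It defines the primary outcome as the change in D/P creatinine from randomization to the end of the 10 months.
- **Exit criteria** opens with "Reasons for permanently discontinuing the study medication are" and ends its list with "5) a severe adverse event".
- **Clinical safety monitoring** begins its definition with "A severe adverse event or reaction is any untoward medical occurrence that" and then gives limbs a) to d), one of which is "c) requires inpatient hospitalization or prolonges an existing hospitalization". Of adverse events in general it says "It does not necessarily have a causal relationship with this treatment", and it names peritonitis among those expected. The reporting rule then changes the word: "Any serious adverse event, whether or not considered related to the study medication".
- **Study medications** (text below Table 1) manages peritonitis within the trial: "treatment will be given intraperitoneally according to international pediatric guidelines", with "a glycopeptide/ceftazidime combination in patients with defined risk factors for severe course and poor outcome". Objectives of the study and Secondary outcome measures make the incidence, severity and course of peritonitis something to be compared between arms.

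**The concern.** Restricting the ANOVA to completers has two consequences.

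First, it leaves out data already collected on the assigned fluid. A child who stops after month 6 has a baseline PET and two on-fluid PETs, none of which enters the ANOVA.

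Second, it selects children by what happens after randomisation. With half the cohort expected to leave, the comparison is between those who remained in each arm, not between the randomised groups. Some exits need not be unrelated to the outcome. Technique failure is an exit reason, and the Background links non-elective termination of PD to loss of ultrafiltration from peritoneal damage. Because the trial is open-label, a discretionary decision to stop is taken by staff who know the fluid.

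Exit criterion 5 contributes a part that could be avoided. Read literally, any admission for an adverse event, related or not, is a reason to stop the fluid permanently. That would include an admission for peritonitis, which the protocol otherwise treats in-study and compares between arms. After transplantation or a switch to haemodialysis a child is no longer on PD. After this kind of exit the child may still be, so a milder rule could have kept the child on the assigned fluid.

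**Working it through.** **The plan's own figure.** 15 per group x 2 = 30 completers, and 30 / (1 - 0.50) = 60 enrolled, as stated. So 30 children are expected to complete and 30 to drop out. How 15 was reached from the assumed effect is a separate question and is not used here.

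**On-fluid PETs in hand at exit** (schedule from Study design): 0 if the child leaves before month 3, 1 if between months 3 and 6, 2 if between months 6 and 10. The baseline PET, done on conventional fluid, is not counted.

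**Timing of exits.** The article does not give it, so two patterns are assumed.

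*Pattern A, constant hazard reaching 50% at month 10:* S(t) = 0.5^(t/10).
- S(3) = 0.812, S(6) = 0.660, S(10) = 0.500
- Exits = 60 x the fall in S: 11.3, 9.1 and 9.6 children in the three intervals

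*Pattern B, 30 exits spread evenly over 10 months:*
- 30 x 3/10 = 9, 30 x 3/10 = 9, 30 x 4/10 = 12

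| | Pattern A | Pattern B |
|---|---|---|
| Exit before month 3 (0 PETs) | 11.3 | 9 |
| Exit in months 3-6 (1 PET) | 9.1 | 9 |
| Exit in months 6-10 (2 PETs) | 9.6 | 12 |
| Children with at least 1 on-fluid PET | 18.7 | 21 |
| Unused on-fluid PETs | 9.15 + 2 x 9.59 = 28.3 | 9 + 2 x 12 = 33 |

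Completers contribute 30 x 3 = 90 on-fluid PETs. Using the rest would add 28.3/90 = 31% to 33/90 = 37%.

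**Share due to criterion 5.** The article gives no rate of admissions or adverse-event exits. If that share of drop-outs is assumed, with the same timing as all exits:

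| Assumed share | Unused on-fluid PETs |
|---|---|
| 0% | 0 |
| 10% | 2.8 to 3.3 |
| 25% | 7.1 to 8.3 |
| 50% | 14.2 to 16.5 |

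Admissions for treatable peritonitis would be only a part of any such share.

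**The wording chain.** Criterion 5 uses the term *severe adverse event* without qualification. Clinical safety monitoring defines that same term by outcome (death, threat to life, admission, disability) and not by intensity. Adverse events need no causal link, and peritonitis is one of those listed. An admission for peritonitis therefore satisfies criterion 5 as written. A child taken off the fluid for it does not complete 10 months and so leaves the ANOVA.

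**The case against.** The strongest reply is that the peritonitis scenario takes the least sensible reading of a five-item list. The list gives reasons for stopping and does not say that every such event must lead to withdrawal. The specific instructions on antibiotics show that peritonitis, including cases at risk of a severe course, is meant to be managed in the trial. A journal article may also leave to the full protocol who decides and whether fluid can be restarted. This stands. A reader might infer that every child admitted with peritonitis must be withdrawn; the article does not say so. What remains is that the term used in the exit list is defined on the page, and that definition includes admission.

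A second reply is that the 28 to 33 PETs cover all causes of exit, and that transplantation is the only cause the sample-size section names. This also stands. The figure measures the completers restriction and must not be read as the effect of criterion 5.

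Third, the Kaplan-Meier strategy keeps everyone who started study fluid, so the trial as a whole does not discard these children. That is correct. But the change over 10 months, which Sample size estimation calls the primary outcome, is addressed more directly by the ANOVA than by time to a threshold, and neither strategy is given priority.

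Fourth, the 50% allowance already budgets for losses. It covers the head count, so no further loss of completers is claimed here. It does not address who is lost.

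Finally, a narrower criterion 5 would still be judged by unblinded staff. That is true, so the wording change is only a supporting edit. The change of model matters more, because a child's earlier PETs then count whatever the reason for exit.

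**Conclusion.** The point holds mainly as a criticism of the completers-only ANOVA. With 50% drop-out expected and PETs scheduled at months 3 and 6, that analysis leaves out roughly 28 to 33 on-fluid PETs from 19 to 21 children, and it conditions a main comparison on a post-randomisation event in an open-label trial. The ranges rest on the planned 50% drop-out and on the two assumed exit patterns.

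Exit criterion 5 is a secondary and avoidable contributor. Its wording permits permanent discontinuation after any admission for an adverse event, but its share of exits is unknown and may be small.

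A reader might go further and conclude that the ANOVA is biased towards one fluid, or that peritonitis admissions will noticeably shrink the trial. The documents support neither: they give no exit rates by arm or by cause, so the size and direction of any bias cannot be derived. The change is worth making because it is specific and cheap.

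**What to change.** 1. Replace the completers-only ANOVA with a repeated-measures mixed model for D/P creatinine, using every available on-fluid PET from all randomised children who started study fluid. Keep the completers analysis as a sensitivity analysis, and do the same for secondary outcomes measured repeatedly.
2. In Clinical safety monitoring, call the a) to d) definition *serious*, in line with the reporting rule.
3. Reword exit criterion 5 so that it covers only adverse events that make continuing the assigned fluid unsafe, and state that admission alone, for example for treatable peritonitis, is not an exit.
4. Treat PETs after stopping the fluid as optional and supplementary for children who remain on PD. They may dilute the buffer contrast: the Background reports that the CA125 effect reversed on return to conventional fluid.

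The cost is a little more analysis work and two wording edits, with no additional visits for items 1 to 3. The mixed model relies on a missing-at-random assumption: given the data already observed, exit must not depend on the unseen D/P values. That should be stated, and the comparison with the completers analysis reported beside it.

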### Study medications

The composition of the study fluids is given in Table 1. Both Bicavera^® ^and Balance will be available in three different glucose concentrations to meet individual ultrafiltration requirements. The fluids will be administered at a dose of approximately 1,100 ml/m^2 ^body surface area per dwell. Both in patients on CAPD and CCPD, the number of cycles and dwell times can be varied according to clinical needs. The dose of dialysis will be tailored individually in order to ascertain a minimum total weekly Kt/V_Urea _of ≥ 2.0.

**Table 1 T1:** 

	Balance 1.5%	Balance 2.3%	Balance 4.25%	Bicavera^® ^1.5%	Bicavera^® ^2.3%	Bicavera^® ^4.25%
Sodium (mmol/l)	134	134	134	134	134	134
Calcium (mmol/l)	1.75	1.75	1.75	1.75	1.75	1.75
Magnesium (mmol/l)	0.5	0.5	0.5	0.5	0.5	0.5
Chloride (mmol/l)	101.5	101.5	101.5	104.5	104.5	104.5
L-Lactate (mmol/l)	35	35	35	-	-	-
Bicarbonate (mmol/l)	-	-	-	34	34	34
Glucose-monohydrate (g/l)	15	23	42.5	15	23	42.5
Osmolarity (mosmol/l)	358	401	511	358	399	509
PH	7.4	7.4	7.4	7.4	7.4	7.4

Any kind of concomitant medication during the run-in period and the study period will be documented in the case report form with respect to type, dosage and mode of delivery. In case of peritonitis (defined by cloudy effluent, white blood cell count greater than 100/mm^3 ^with more than 50% polymorphonuclear leukocytes), treatment will be given intraperitoneally according to international pediatric guidelines [24] using cefazoline and ceftazidime in patients with mild peritonitis and a glycopeptide/ceftazidime combination in patients with defined risk factors for severe course and poor outcome.

Bicarbonate supplementation will be discontinued at start of the run-in period and only re-instituted if blood bicarbonate levels drop below 17 mmol/l despite sufficient dialysis efficacy. The recommended dosage is 0.5 mmol/kg/day divided into 3 doses.

### Clinical safety monitoring

An adverse event is defined as any untoward medical occurence in a patient who takes the study medication. It does not necessarily have a causal relationship with this treatment. This may be an unfavourable and unintended sign, symptom or disease, which is observed after exposure to the study medication, whether or not considered related to the treatment. Moreover, the participating investigators will report all treatment-emergent adverse events that are observed on the online adverse event form. This applies regardless of the clinical significance or the assessment of study drug causality. In this trial, such adverse events may include inflow pain, severe changes of the state of hydration, abnormal electrolyte and glucose blood levels, peritonitis, abdominal hernia, and allergic reactions.

A severe adverse event or reaction is any untoward medical occurrence that a) results in death, b) is life-threatening, c) requires inpatient hospitalization or prolonges an existing hospitalization, or d) results in persistent or significant disability/incapacity.

Any serious adverse event, whether or not considered related to the study medication, and any unexpected drug reactions with significant hazard to the patient population will be reported to the responsible safety assessor at Fresenius Medical Care by phone or by fax within 24 hours following first knowledge of the event. Alternatively the clinical monitor may be informed. This information will be forwarded to and evaluated by the safety monitoring committee, and reports of serious adverse reactions will be disseminated to all participating centers for submission to their respective institutional review boards. Fresenius Medical Care is responsible for passing on the information to relevant supervisory authorities.

### Data management

Data acquisition will be entirely through the internet. The case report form menus will be used to record the following: 1) baseline clinical patient information, 2) physical and biochemical examination variables, 3) study and concurrent medications, and 4) adverse events.

Periodic computerized audit reports will be run to monitor data quality and completeness. The data base is stored on a server drive that is backed up to tape daily by Tel-A-Vision, Media Networking GmbH.

In order to insure confidentiality, data from each patient will be recorded in the computer data base with a unique contributing center code, study code, sequence number and patient initials. Patient names are never entered online or forwarded in any other form to the coordinating office.

### Sample size estimation

The primary study outcome is the change in 4h-D/P_Cr _from the time of randomization to the conclusion of the 10-month study period. In a previous trial we demonstrated a 6% increase of D/P_Cr _in children on lactate-buffered PD fluid in contrast to a 4% decrease in D/P_Cr _using bicarbonate buffered fluid within 3 months of exposure, resulting in a statistically significant 10% difference in the evolution of peritoneal creatinine transport rate [13]. Assuming that this effect was at least in part due to the different buffer substances applied, a difference in D/P_Cr _at least 7 ± 10% can be expected when Balance and Bicavera^® ^are applied for 10 months. To detect this difference with a sensitivity of 80% and an error probability of 5%, at least 15 patients per randomization group will be required. Assuming a 50% drop-out rate due to renal transplantation and other reasons in the course of the study, 60 patients will have to be enrolled.

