### Study design

This is a multicenter open-labelled, controlled, randomized clinical trial, designed to test the effects of the buffer substance in biocompatible PD fluids on peritoneal small solute transport capacity. All subjects will undergo a 2-month run-in period, in which they receive conventional lactate buffered, acidic, GDP containing PD fluid. During this period, patient eligibility for the trial will be verified and the dialysis dose will be optimized if necessary to ensure appropriate PD adequacy. At the end of this period, the patients will be stratified according to residual renal function (greater or less than 100 ml urine output/day/1.73 m^2^) and the type of phosphate binder therapy (Sevelamer vs. calcium-containing phosphate binders), since these variables may affect the overall efficacy of metabolic acidosis control. Following stratification, subjects will be randomized centrally to receive either the lactate-containing Balance solution or the bicarbonate buffered Bicavera^® ^solution for a period of 10 months. Both during the run-in period and during the intervention phase, patients will be monitored by monthly clinical and laboratory examinations, including capillary blood gas analyses. In addition, peritoneal equilibration tests (PETs), 24-hour dialysate and urine collections and intraabdominal pressure assessments will be performed at time of randomization (with conventional PD fluid) and after 3, 6 and 10 months of treatment (with the study solutions). Also, peritoneal biopsies will be performed on occasion of intraabdominal sugery or laparoscopy prior to start and after termination of the study (usually at time of catheter insertion and renal transplantation).

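### Fifteen evaluable patients per group give about 46% power, not 80%, for a difference of 7% with an SD of 10%

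*Protocol article*

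**What the plan says.** All of this is in the protocol article.

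- **Study design:** the trial is a "multicenter open-labelled, controlled, randomized clinical trial" with two fluids given in parallel.
- **Sample size estimation, outcome:** the trial is sized on the change in 4-hour D/P creatinine "from the time of randomization to the conclusion of the 10-month study period".
- **Sample size estimation, effect:** an earlier trial by the same group found a 6% rise on lactate-buffered fluid and a 4% fall on bicarbonate-buffered fluid, a difference of 10%. Since the buffer may explain only part of this, the section reduces the expected difference to "at least 7 ± 10% can be expected when Balance and Bicavera" are given for 10 months.
- **Sample size estimation, result:** "with a sensitivity of 80% and an error probability of 5%, at least 15 patients per randomization group will be required".
- **Sample size estimation, enrolment:** "Assuming a 50% drop-out rate due to renal transplantation and other reasons in the course of the study", the target becomes 60 patients.
- **Statistical approach:** the first strategy is a repeated-measures ANOVA restricted to patients who complete the 10 months on study fluid.

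The sample size section names no test, does not say whether the 5% is one- or two-sided, does not say what the ± denotes, and assumes no correlation or other variance reduction.

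**The concern.** A difference of 7 with an SD of 10 is a standardised difference of 0.7. Comparing two independent groups at that effect size with 80% power needs clearly more than 15 patients in each, so the printed figure looks about half of what it should be.

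The shortfall falls on the first-listed analysis of the primary outcome. After the assumed 50% drop-out, the completers entering the repeated-measures ANOVA are the 15 per group in question. If power there is near one half, a true 7% effect would be missed about as often as found. The trial exists to settle whether the buffer matters in neutral-pH, low-GDP fluids. A null result from a design believed to have 80% power could be taken as evidence that it does not.

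**Working it through.** **Inputs** (Sample size estimation): difference δ = 7; SD σ = 10, reading the ± as the per-patient SD of the change within a group; power 80%; error probability 5%; 15 per group. The two-sample structure comes from Study design. Sidedness is not given, so both versions are shown.

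**The plan's own enrolment step.** 2 × 15 = 30 evaluable; 30 / (1 − 0.50) = 60. This reproduces. The error lies before it, in the 15.

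**Required size, two-sample.** n per group = 2 (z₁₋α + z₁₋β)² (σ/δ)², with α/2 in place of α for a two-sided test.

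- Two-sided: 2 × (1.960 + 0.842)² × (10/7)² = 32.04, so 33. The exact t-test gives 33.02, so 34.
- One-sided: 25.2, so 26. The exact t-test gives 25.94, so 26.

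The stated 15 is not reproduced either way.

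**Power with 15 per group.** By the normal approximation, two-sided: 0.7 × √(15/2) = 1.917; 1.917 − 1.960 = −0.043; Φ(−0.043) = 0.483.

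| | Two-sided | One-sided |
|---|---|---|
| Normal approximation | 48.3% | 60.7% |
| Exact t-test | 45.7% | 58.9% |

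**What 15 per group can detect** (t-test, 80% power, SD 10): a difference of 10.6% two-sided or 9.3% one-sided. Conversely, to detect 7% the SD would have to be about 6.6% two-sided or 7.5% one-sided.

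**If nobody dropped out** (30 per group, t-test): 76% two-sided, 85% one-sided.

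**Enrolment implied by the stated inputs at 50% drop-out:** two-sided, 66 to 68 evaluable and 132 to 136 enrolled; one-sided, 52 evaluable and 104 enrolled.

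**Readings that come near 15.** Sizes are per group for 80% power, except the one-sample row, which is a total.

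| Reading | Two-sided (normal / t) | One-sided (normal / t) |
|---|---|---|
| One-sample or paired formula, δ = 7, SD 10 | 17 / 19 | 13 / 15 |
| ± is the SD of the difference between two patients, so per-group SD = 10/√2 = 7.07 | 17 / 18 | 13 / 14 |
| δ = 10, SD 10 | 16 / 17 | 13 / 14 |

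The first does not fit two parallel groups. It leaves out the factor 2 in the formula above, which may be how 15 arose, though that is inference. The second is not stated in the text; with 15 per group it gives 74% (t) or 77% (normal) two-sided and 84% (t) one-sided. The third uses a difference that the section itself reduces to 7.

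**The case against.** The best case against the point is that its central input is an interpretation. The text attaches the ± to the difference and never calls 10% a per-group SD. If it is the SD of a difference between two patients, 15 per group gives 74% two-sided and 84% one-sided. The hypothesis under Objectives of the study is directional, so a one-sided test is conceivable, and under both readings together 15 would suffice. This stands as a reason to make the 46% conditional and to ask first what was meant. It does not rescue the paragraph: it needs two unstated assumptions at once, and neither alone gets 15 per group to 80%.

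Second, the planned analysis is a repeated-measures ANOVA over PETs at randomisation and months 3, 6 and 10, with possible covariates, and not a t-test on change. It could be more precise. But no correlation is stated, and the gain would have to be large. If 10% were the SD before adjustment, a correlation of 0.5 gives 25 per group and 0.7 gives 17 (normal approximation, two-sided). Reaching 15 needs r² = 1 − 15/32.04 = 0.53, so r of about 0.73. The Kaplan-Meier strategy does use all patients started on study fluid, but the calculation is not for that endpoint.

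Third, the protocol makes no equivalence claim, so a commitment on how a null result is reported goes beyond correcting the arithmetic. That is fair; the commitment is a safeguard that follows from the low power. Finally, a fuller protocol may define the ± and the test. Even so, the published paragraph gives a sample size that its printed inputs do not support.

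**Conclusion.** The sample size statement is wrong as written. Taking 10% as the per-group SD of the change and testing two-sided at 5%, 15 evaluable patients per group give about 46% power for a 7% difference; 80% needs 33 to 34. One-sided, the power is about 59% and the requirement 26. If the 10% is instead the SD of a between-patient difference, two-sided power is 74% and the requirement 17 to 18. Power of 80% is reached only when that reading is combined with a one-sided test, and the document states neither.

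Under the ordinary two-sided reading, the trial as sized has 80% power only for a difference of about 10.6%. That is larger than the 10% of the earlier trial, which by the Background section compared fluids differing in pH and GDP content as well as buffer, and which the protocol itself does not expect to see again. The drop-out inflation from 30 to 60 is correct.

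**What to change.** Rewrite the calculation in Sample size estimation so that it:

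1. names the test and its sidedness;
2. says what the ± 10% is (per-group SD of the change, SD of a difference, or other) and, if a smaller SD or a correlation was intended, gives its value; a 7% difference with 80% power at 15 per group, two-sided, needs an SD of about 6.6%;
3. if the 10% is the per-group SD, states that 15 evaluable per group give about 46% power for 7% (two-sided) and 80% power for about 10.6%;
4. states that a non-significant result will be reported with its confidence interval and not read as showing that the buffer makes no difference.

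Some precision may be regained at no cost in patients by analysing all randomised patients in a model that adjusts for baseline D/P creatinine and uses the month 3 and month 6 PETs, instead of completers only. The gain cannot be put in figures from the document. It should not be counted on to restore 80%, because even 30 evaluable per group give 76% in a plain two-sided comparison.

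The cost is one reworded paragraph and a less favourable stated power. No extra patients are needed unless the sponsor chooses to keep 80% power for 7%, which at 50% drop-out would mean enrolling about 132 to 136.
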